#### Six months of follow-up

For all participants, the medication use will be recorded before randomization and repeated at least 6 months later. At a 6-month follow-up, research pharmacists will revisit participants and ascertain medication usage in both study arms using the same processes as the baseline review. To avoid bias and achieve blinding of the visiting pharmacist, each participant will be visited by a different pharmacist at follow-up than the one who saw them at baseline. The post-intervention medication review will be provided to the participants’ GP for information purposes only.

### Data management

#### Data collection methods

All observations and results will be recorded in custom-designed Research Electronic Data Capture (REDCap https://www.project-redcap.org/) databases hosted at the University of Otago, Christchurch, New Zealand, which will allow for secure online data entry from multiple sites into a central data repository [30, 31].

A REDCap database holding details on potential study participants will contain identifying personal data separate from the database holding de-identified data for consented study participants. Access to these databases is defined in the section “Access to data.”

Data will be collected at the time of the interRAI assessment (T0), during the preparation of the intervention (T1), at least 6 months following the baseline pharmacist’s review (T2), and at the end of the study period or end of study participation for admission into aged residential care or death (T3) as detailed in Table 2.

**Table 2 Tab2:**
[figure not shown]
Participant data to be collected during the study

*T0* time of participant’s interRAI assessment, *T1* intervention preparation, *T2* 6 months following baseline pharmacist’s review, *T3* end of study period/end of study participation, *(X)* denotes optional completion if activity was not performed at T0

The medication use will be recorded before randomization and repeated at 6 months of follow-up. Secondary health information such as mortality, hospital admissions, and fractures will be obtained from the health provider and the New Zealand Ministry of Health. These data will be linked with the study data using each participant’s unique National Health Index (NHI) number [32].

No biological samples will be collected in this trial.

#### Data entry and quality checks

The pharmacist will record the medication review details on paper during the participant interview and perform the DBI calculations. After the visit, the pharmacist will transfer the data into the REDCap database, including a scanned version of the corresponding paper record. The study’s data manager will facilitate the review process by informing the senior pharmacist to review the DBI calculation and records. Upon successful review or correction of any errors, the record in REDCap will be locked.

After completing the trial, the data manager will export all data from REDCap, de-identify the records, check for missing values, outliers, and inconsistencies before passing the data to the study’s statistician for analysis. The analysis process will include further checks, such as range tests and outliers in computed and outcome values. Once the dataset’s quality is confirmed by the study’s data manager and statistician, the dataset will be locked.

To facilitate medication specific analyses, the dataset containing individual medication and medication use details will undergo post-processing to achieve consistency with medication names, dosage, units of measure and recording of “as needed” (PRN) medications. In addition, other relevant pharmaceutical data such as chemical compound identifiers or medication costs may be added to the dataset.

#### Outcome data

The dataset for analysis will include all interRAI assessments, admissions into residential care, hospital admissions, mortality, and the New Zealand Pharmaceutical Management Agency (PHARMAC) dispensing records. These will be classified into several groups as follows:
Demographic datainterRAI™ assessment datainterRAI™ scales and Clinical Assessment Protocols (CAPs)New interRAI™-based frailty indicesDrug Burden Indices (DBI)Medical and pharmaceutical notes that support the pharmacist deprescribing reviewsAdmissions into aged residential careNew Zealand mortality dataDispensing records from PHARMACEmergency department presentations and hospital admissions

Data from consented participants will be linked using each participant’s unique study ID. The final de-identified dataset will be provided to the study statistician for analysis. The dataset will be archived upon completion of the study.

#### Access to data

The study data manager will have full unrestricted access to all study data throughout the trial. The study administrator and study pharmacists will have access to personal details to facilitate recruitment, consenting, and booking visits to participants. No other member of the research team will have access to personal details of study prospects or study participants. The senior pharmacist will have restricted access to data as required to perform data review duties throughout the trial. As a member of the Data Monitoring Group, the study statistician will have access to raw data held in REDCap to perform data quality checks. Blinding will be maintained throughout the trial.

After completing the trial and locking of data, the primary investigator and other named members of the research team will have access to de-identified study data. Data will not be shared with other researchers as per ethics approval and participant consent.

### Outcomes

In this study, five outcome scenarios are possible: (1) completion of the trial, (2) entry into aged residential care (ARC) before completion (this would be linked to a change in GP and medication control), (3) prolonged hospitalisation, (4) death, and (5) withdrawal or other loss to follow-up. The first two outcome scenarios would involve the post medication review being undertaken either with the participant or via the medical records of a care facility. The third outcome scenario could lead to delays in recording the post-intervention review or may lead to any of the four other scenarios.

#### Primary outcome

The primary outcome will be the change in a participant’s DBI (ΔDBI) between the time of the baseline interRAI assessment (T1) and the time of 6 months of follow-up (T2; ΔDBI = DBI_T1_ – DBI_T2_). Data for the calculation will be collected by comparing medication use pre-and post-intervention. We will determine if there is a greater reduction in the DBI of participants in the experimental arm of the trial compared with participants with the same level of frailty in the control arm. Subgroup analysis will determine if deprescribing is more pronounced for those with more severe frailty.

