## Methods

### Hypotheses and aims

We hypothesize that implementing a pharmacist-led medication review and provision of deprescribing recommendations to general practitioners (GP) will reduce the use of anticholinergic and sedative medications in community-dwelling older people compared to the control arm overall and that the reduction will be more pronounced for older people with a greater level of frailty. Thus, the primary objective is to determine if pharmacist-led medication reviews focused on reducing anticholinergic and sedative medications lead to GPs deprescribing these medications for older people living in the community. The secondary objective is to determine if a frailty measure based on data collected in the interRAI Home Care [24] and Contact assessment [25] can identify a group of older people who could benefit the most from deprescribing.

The interRAI is a comprehensive assessment database system utilized internationally and in New Zealand to standardize the evaluation of complex care needs of older people. It is routinely used to collect data regarding patients’ medical and functional status [26]. In New Zealand, the comprehensive Home Care assessment [24] is used for persons seeking admission into publicly funded aged residential care, while the shorter contact assessment [25] is for home-based support services. The reliability of the interRAI™ has been tested, and it has been shown to meet or exceed the standard cut-offs for acceptable reliability [27].

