Lorazepam	N05BA06	Zolpidem	N05CF02
Lormetazepam	N05CD06	Zuclopenthixol	N05AF05
Methadone	N07BC02		

After enrolment, participants will be stratified using a frailty index (FI), which will be based on a cumulative deficit model using 15 relevant items common to the interRAI Homecare and Contact assessments. Cut-off values for each stratum will create three equal-sized frailty strata based on New Zealand interRAI HC and CA data used for developing the frailty index. Participants will be stratified into one of three frailty strata (low, medium, high) and allocated in a 1:1 ratio within each strata to the intervention and control arms of the trial.

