### Statistics methods

#### Power and sample size

For this RCT, we define the clinically significant change in DBI as 0.5, the equivalent of one medication contributing to DBI given at the minimal efficacious dose [14]. Approximately 4% of recent interRAI assessments show a ΔDBI ≥ 0.5 over 6 months. Therefore, a meaningful outcome from deprescribing in this study would be to increase the percentage, in the intervention cohort, with a DBI change ≥of 0.5 by 10% points. This would bring the percentage ΔDBI ≥ 0.5 over a 6-month period to 14%.

The null hypothesis is that there is no difference in proportions with a ΔDBI of ≥ 0.5 over 6 months between the control and intervention groups, given that 4% of participants in the control group have a ΔDBI of ≥0.5. Therefore, to disprove the null hypothesis, we need to detect a change in the number of participants of 10% or more with a ΔDBI of ≥0.5 with a power of 90% at an *α*=0.05. This requires 167 participants in each arm of the study, 334 in total.

For each frailty stratum under the null hypothesis, there will be no difference in change in DBI between the control and intervention groups and assume 4% of participants in the control group have a reduction in DBI of ≥0.5, then to detect a change in the number of participants of 20% or more with a reduction in DBI of ≥0.5 with a power of 80%, and at *α*=0.017 (0.05/3), requires 56 participants in each arm of the study (112 in each stratum, 336 in all).

It is estimated that over 12 months within the target areas of the district health boards’ approximately 650 participants will meet the basic inclusion criteria, including the minimum DBI. In addition, previous data suggest that approximately 50% of the study’s cohort will take the target medicines, and therefore, 325 people would be eligible to take part in the study per annum.

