#### Statistical analysis

The data analysis will use the intention-to-treat principle (where all available data, including records showing non-adherence to the protocol, from participants will be included in the analysis). Thus, imputation will not be used for missing data.

We will compare the proportions of the outcome measures using a chi-squared test and present results with a 95% confidence interval.

We will present Kaplan-Meier survival curves for analysis of hospitalizations, emergency department visits, entry into aged residential care, and mortality within subgroups. Subgroups will include control low frailty, control medium frailty, control high frailty, intervention low frailty, intervention medium frailty, and intervention high frailty. The analyses will be controlled for age and sex, with death as a censored event. We will then conduct a competing risk analysis using cumulative incidence functions (CIF). For example, where entry to aged residential care is the primary event of interest, death is the competing event. The CIFs are the probability of observing these events before the end of the 6-month follow-up period.

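### The frailty hypothesis is an arm-by-frailty interaction, but the only frailty tests described for DBI compare arms within each stratum; nor is the counted 112 per stratum assured

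*Protocol article*

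**What the plan says.** **Hypothesis.** Hypotheses and aims predicts a fall in DBI medicine use against control overall, and that "the reduction will be more pronounced for older people with a greater level of frailty". Finding the group that benefits most is the secondary objective, and the Discussion presents this as the distinctive feature of the design.

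**Analysis.** Primary outcome describes a comparison of the experimental arm "compared with participants with the same level of frailty in the control arm", then adds: "Subgroup analysis will determine if deprescribing is more pronounced for those with more severe frailty". Statistical analysis says "We will compare the proportions of the outcome measures using a chi-squared test", and Table 3 lists the same test for the proportion with a DBI change of at least 0.5.

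**Sizing.** In Power and sample size, the null for each stratum is that "there will be no difference in change in DBI between the control and intervention groups". The inputs are a 4% control rate, a 20% change, 80% power and alpha 0.017 (0.05/3). The result "requires 56 participants in each arm of the study (112 in each stratum, 336 in all".

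**Strata.** Study design states: "Cut-off values for each stratum will create three equal-sized frailty strata based on New Zealand interRAI HC and CA data". Participants then excludes, among others, people with no deficits on the index, people with dementia or a Cognitive Performance Scale score of 3 or more, and people with DBI below 0.5. No quota per stratum is given.

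**The concern.** A claim that the effect grows with frailty is a claim about a difference between arm differences. Three separate tests of no arm difference do not address it. One stratum can reach significance and another miss it by chance alone when the true effects are equal, and real differences between strata can be present when all three tests agree.

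What is at stake is the secondary objective. The Cost-benefit analysis section anticipates identifying a frailty level that gains most from targeted reviews. A pattern of p-values read as a gradient could steer that conclusion with no test behind it. The stated 80% power also applies to the within-stratum question, and only if each stratum reaches 56 per arm.

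**Working it through.** **Inputs from Power and sample size.** Control rate 4%; overall target 14%; stratum change of 20%, read as percentage points (4% v 24%) to match the overall calculation; alpha 0.017; 56 per arm per stratum. Tests are taken as two-sided, which fits the stated figures, and every participant is assumed to have a follow-up DBI.

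**Step 1: reproduce the plan's figures.** Unpooled two-proportion formula, n = (z_alpha + z_power)² × [p1(1−p1) + p2(1−p2)] / d².
- Overall: (1.960 + 1.282)² × (0.0384 + 0.1204) / 0.10² = 166.9, so 167 per arm, as stated.
- Stratum: (2.387 + 0.842)² × (0.0384 + 0.1824) / 0.20² = 57.5, so 58 per arm against the stated 56. The arcsine formula gives 55.

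The 56 is therefore a within-stratum size. Exact enumeration of the uncorrected chi-squared test at 56 per arm gives power of 0.80 for 4% v 24% and 0.30 for 4% v 14%.

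**Step 2: separate tests when the effect is the same in all strata.** Let p be the power of each independent stratum test.
- High significant and low not: p(1−p).
- Any disagreement among the three: 1 − p³ − (1−p)³.

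| Common effect | p | High significant, low not | Any disagreement |
|---|---|---|---|
| 4% v 24% | 0.80 | 0.80 × 0.20 = 16% | 1 − 0.512 − 0.008 = 48% |
| 4% v 14% | 0.30 | 0.30 × 0.70 = 21% | 1 − 0.027 − 0.343 = 63% |

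The third column is the pattern that would wrongly seem to support the hypothesis. The last column also counts patterns that contradict it.

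**Step 3: power of a test that does address the hypothesis.** High-versus-low difference in risk differences, two-sided 0.05, control rate 4% in both strata, 56 per arm per stratum:

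SE = √{[pH(1−pH) + pL(1−pL) + 2 × 0.04 × 0.96] / 56}, power = Φ(|pH − pL| / SE − 1.96).

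The documents give no stratum-specific intervention rates. The low-stratum rates below are assumptions, with pH = 24%.

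| Effect, low v high (points) | SE | Difference / SE | Power | Per arm per stratum for 80% |
|---|---|---|---|---|
| +10 v +20 | √(0.3796/56) = 0.0823 | 1.21 | 23% | 298 |
| +5 v +20 | √(0.3411/56) = 0.0780 | 1.92 | 48% | 119 |
| 0 v +20 | √(0.2976/56) = 0.0729 | 2.74 | 78% | 59 |

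Even with no effect at all in the low stratum, power stays just under 80%.

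**Step 4: stratum sizes.** The documents give no frailty distribution for eligible people, so these splits of 336 are assumptions. Power is for 4% v 24% at alpha 0.017 by the pooled normal formula, which reads somewhat low: it gives 76% where exact enumeration gives 80%.

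| Split (low/medium/high) | Participants | Power |
|---|---|---|
| Equal thirds | 112 / 112 / 112 | 76% / 76% / 76% |
| 25/35/40 | 84 / 118 / 134 | 60% / 78% / 84% |
| 20/35/45 | 67 / 118 / 151 | 49% / 78% / 89% |

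A 25/50/25 split gives 42, 84 and 42 per arm. By exact enumeration that is about 64% power in the two outer strata and 94% in the middle one.

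**The case against.** **The analysis is not fully fixed.** Alpha 0.017 appears only in the sample-size paragraph, the term subgroup analysis is not defined further, and no rule says a gradient will be read from separate p-values. A journal article may leave the subgroup model to the analysis plan. This stands as far as it goes: an interaction test could still be named there. But the article does commit to a frailty hypothesis, stratum nulls, a divided alpha and a stratum sample size, and all of these belong to the within-stratum question. A later interaction test would inherit the power in Step 3.

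**Stronger readings that the documents do not support.**
- A reader might infer that the cut-offs will fail to give 112 per stratum. This is not shown. The documents do not say whether people with zero deficits were in the reference data, and the exclusions may pull both ways: removing zero deficits could thin the low stratum, while the cognitive, dementia and terminal-illness exclusions may thin the high one.
- A reader might take 48% to 63% as the rate of false frailty gradients. Those figures count every disagreement. The pattern that mimics the hypothesis occurs in 16% to 21%.
- A reader might infer serious inflation of family-wise error from an overall test at 0.05 beside three at 0.017. Normal test statistics would give about 8.3%. At the plan's own 4% rate the stratum tests are conservative (actual size about 0.006), and simulating all four tests gives about 5.9%. The article also labels the overall question primary and frailty secondary, though it states no formal testing order.

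**Conclusion.** The point holds in a bounded form. The frailty hypothesis calls for an arm-by-frailty comparison, and the only inferential frailty comparisons described for DBI are within-stratum arm tests, sized and alpha-adjusted one stratum at a time. With equal true effects and 56 per arm, these would show a misleading high-but-not-low result in about 16% to 21% of trials. A direct contrast has roughly 23% to 78% power over the assumed gradients.

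On stratum size, the supported conclusion is that 112 is not assured: the cut-offs are thirds of a national reference dataset, eligibility is narrower, and no quota is stated.

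These figures rest on a 4% control rate in every stratum, two-sided tests, 20% read as percentage points, and complete follow-up. The overall comparison and its 167 per arm, which reproduce exactly, are not in question.

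**What to change.** Before the statistician is unblinded:

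1. Analyse the frailty objective in one model with arm, frailty and an arm-by-frailty term. Frailty may enter as a stratum score or as the continuous index; either meets the point, but fix the choice in advance.
2. Report the difference in effect with its 95% CI, and show stratum results as descriptive estimates with intervals.
3. Keep the overall test primary at 0.05.
4. State the power of the interaction test for a range of gradients, and acknowledge that it is below the 80% quoted for the stratum tests.
5. State that 112 per stratum is not assured, and give per-stratum power over a range of plausible splits.

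The cost is wording and a short calculation; no new data or visits are needed. The downside is a less favourable stated power for the frailty question, so an inconclusive interaction result would have to be reported as inconclusive.

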#### Secondary outcomes

Secondary outcomes measures will be compared between the two arms of the trial after 6 months and are outlined in Table 3. From the funder’s perspective, these include the number of hospitalizations, emergency department visits, entry into aged residential care, all-cause mortality, and cost-utility. In addition, we will measure the number of emergency department visits and unplanned hospital admissions. Data on entry into or change in the level of care in aged residential care will be extracted from relevant national databases by the analytical services of the Ministry of Health. Patient mortality data will be matched using participants’ National Health Index (NHI) number, added to the dataset, and analyzed using competing risk regression. In a separate analysis, we will conduct a health cost utility assessment.

**Table 3 Tab3:** Outcome measures and analysis

Outcome	Measure	Alternative hypothesis	Analysis
Drug burden change	Proportion ΔDBI ≥ 0.5	Intervention greater	*χ*^2^ comparison of proportions
Emergency department visits	Proportion	Remain the same or decrease	*χ*^2^ comparison of proportions
Unplanned hospital admissions	Proportion	Remain the same or decrease	*χ*^2^ comparison of proportions
Admissions into aged residential care	HR	Remain the same or decrease	CRRA
Mortality	HR	Remain the same or decrease	CRRA

*ΔDBI* change in Drug Burden Index, *WSR* Wilcoxon signed-rank test, *CRRA* competing risk regression analyses, *χ*^2^ chi-square

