### Study design

This will be a pragmatic two-arm randomized controlled superiority trial to test general practitioner uptake of pharmacist recommendations to deprescribe anticholinergic and sedative medications that are causing adverse side effects in patients. The cumulative use of anticholinergic and sedative medications listed in Table 1 for each participant will be quantified using the DBI [14]. New Zealand registered pharmacists will use previously pilot-tested deprescribing guidelines to recommend to GPs sedative and anticholinergic medications with a potential to be deprescribed [28, 29].

**Table 1 Tab1:** Anticholinergic and sedative medications

Generic medicine name	ATC code	Generic medicine name	ATC code
Alprazolam	N05BA12	Methyldopa	C02AB01
Amitriptyline	N06AA09	Metoclopramide	A03FA01
Aripiprazole	N05AX12	Mianserin	N06AX03
Amantadine	N04BB01	Mirtazapine	N06AX11
Benztropine	NO4AC01	Moclobemide	N06AG02
Benzhexol	N04AA01	Morphine	NO2AA01
Biperidin	N04AA02	Nitrazepam	N05CD02
Buprenorphine	N02AE01	Nortryptyline	N06AA10
Buspirone	N05BE01	Olanzapine	N05AH03
Carbamazepine	N03AF01	Orphenadrine	N04AB02
Cetirizine	R06AE07	Oxazepam	N05BA04
Chlorpheniramine	R06AB05	Oxybutynin	G04BD04
Chlorpromazine	N05AA01	Oxycodone	N02AA05
Citalopram	N06AB04	Paroxetine	N06AB05
Clemastine	D04AA14	Pericyazine	NO5AC01
Clomipramine	N06AA04	Phenobarbital	N03AA02
Clonazepam	N03AE01	Phenytoin	N03AB02
Clonidine	S01EA04	Pizotifen	N02CX01
Codeine	R05DA04	Pramipexole	N04BC05
Cyproheptadine	R06AX02	Prazosin	C02CA01
Darifenacin	G04BD10	Pregabalin	N03AX16
Dexchlorpheniramine	R06AB02	Primidone	N03AA03
Dextromethorphan	N02AC04	Prochlorperazine	N05AB04
Diazepam	N05BA01	Promethazine	R06AD02
Dihydrocodeine	N02AA08	Quetiapine	NO5AH04
Diphenhydramine	D04AA32	Risperidone	N05AX08
Disopyramide	C01BA03	Ropinirole	N04BC04
Doxazosin	C02CA04	Selegiline	N04BD01
Dothiepin	N06AA16	Sertraline	N06AB06
Doxepin	N06AA12	Solifenacin	G04BD08
Escitalopram	N06AB10	Tamsulosin	G04CA02
Fentanyl	N02AB03	Temazepam	N05CD07
Fexofenadine	R06AX26	Terazosin	G04CA03
Flunitrazepam	N05CD03	Tolterodine	G04BD07
Fluoxetine	N06AB03	Tramadol	NO2AX02
Fluphenazine	NO5AB02	Tranylcypromine	N06AF04
Fluvoxamine	N06AB08	Triazolam	N05CD05
Gabapentin	N03AX12	Trifluoperazine	N05AB06
Haloperidol	N05AD01	Trihexyphenidyl	N04AA01
Imipramine	N06AA02	Trimipramine	N06AA06
Lamotrigine	N03AX09	Valproic Acid	N03AG01
Levetiracetam	N03AX14	Venlafaxine	N06AX16
Loperamide	A07DA03	Ziprasidone	N05AE04
Loratadine	R06AX13	Zopiclone	N05CF01

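### For four secondary outcomes, Table 3's alternative hypothesis includes no difference, which is the null of the test assigned, so a non-significant result fits it and no non-inferiority margin is given

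*Protocol article*

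**What the plan says.** Table 3 of the protocol article (Secondary outcomes) has a column for the alternative hypothesis. For emergency department visits, unplanned hospital admissions, admissions into aged residential care and mortality, the entry is the same: "Remain the same or decrease". The first two are to be analysed as proportions with a chi-squared comparison. The last two are to be analysed as HRs from "competing risk regression analyses".

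The DBI row of the same table has a strict alternative, "Intervention greater". The only null written out in the article is for that outcome, under Power and sample size: "The null hypothesis is that there is no difference in proportions with a ΔDBI of ≥ 0.5 over 6 months". Study design describes a "pragmatic two-arm randomized controlled superiority trial".

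Under Statistical analysis the article adds: "We will compare the proportions of the outcome measures using a chi-squared test and present results with a 95% confidence interval". It promises no interval for the HRs and gives no non-inferiority margin for any outcome.

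**The concern.** An alternative hypothesis should be a statement that the data can support by rejecting the null. Here it is the union of the null (no difference, or HR = 1) and a decrease. Rejecting equality in favour of a decrease fits it, failing to reject equality fits it, and only a significant increase goes against it. A test of difference cannot establish sameness. To show that events did not increase, one needs a margin and a confidence limit that excludes it.

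These outcomes matter for what the trial can say about harm. Under Clinical responsibility, reasons for withdrawal other than death are not to be recorded, and hospital admissions are named as something the team will analyse. The Cost-benefit analysis section also counts avoided admissions and avoided entry into residential care as benefits. If the table's wording carries over into the report, a merely imprecise result could be described as agreeing with the hypothesis.

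**Working it through.** **1. Hypothesis against test (logic only).**

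| Outcome | Stated alternative | Assigned analysis | Null of that analysis |
|---|---|---|---|
| Emergency department visits | difference ≤ 0 | chi-squared | difference = 0 |
| Unplanned admissions | difference ≤ 0 | chi-squared | difference = 0 |
| Residential care entry | HR ≤ 1 | competing-risk regression | HR = 1 |
| Mortality | HR ≤ 1 | competing-risk regression | HR = 1 |

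In each row the null lies inside the alternative. The complement of the alternative is an increase, so the matching test would take an increase as its null. That is a non-inferiority test, and it needs a margin.

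**2. The plan's own sample size.** Inputs from Power and sample size: 4% against 14%, "with a power of 90% at an *α*=0.05". With two-sided 0.05 and unpooled variance,

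n = (1.960 + 1.2816)² × [0.04×0.96 + 0.14×0.86] / 0.10² = 10.507 × 0.1588 / 0.01 = 166.9, rounded up to 167 per arm.

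The stated figure reproduces as the size for a two-sided test of difference on the DBI outcome. No size is derived for the four outcomes in question.

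**3. What 167 per arm can show on them.** The article gives no event rates for these outcomes, so every rate below is assumed. The test is two-sided at 5%.

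Power = Φ[(d − 1.96·SE₀)/SE₁], where SE₀ = √(2p̄(1−p̄)/167) and SE₁ = √([p₁(1−p₁) + p₂(1−p₂)]/167).

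- 30% to 38%: SE₀ = 0.0518, SE₁ = 0.0517; (0.08 − 0.1016)/0.0517 = −0.418; power 34%.
- 6% to 10%: SE₀ = 0.0297, SE₁ = 0.0296; (0.04 − 0.0582)/0.0296 = −0.614; power 27%.

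The same formula over a range:

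| Control rate | Power, true 5-point rise | Power, true 10-point rise |
|---|---|---|
| 10% | 28% | 73% |
| 20% | 19% | 56% |
| 30% | 16% | 48% |

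Half-width of the 95% interval when the arms do not differ, 1.96·√(2p(1−p)/167): 9.8 points at 30%, 8.6 at 20%, 5.1 at 6%.

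For an HR with D events split evenly, the 95% interval spans a factor exp(1.96×2/√D) either way. With an assumed 20 events this is 2.4. Power for a true HR of 1.5 is Φ(½√D·ln 1.5 − 1.96): 15% at 20 events and 30% at 50.

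**4. What a not-worse claim would take.** For one-sided 0.025, 80% power and no true difference, n per arm = (1.960 + 0.8416)² × 2p(1−p)/margin². Both margins are assumed for illustration only.

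| Control rate | 5-point margin | 10-point margin |
|---|---|---|
| 10% | 566 | 142 |
| 20% | 1005 | 252 |
| 30% | 1319 | 330 |

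At 167 per arm the planned size would suffice in only one of these six cases.

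**The case against.** The strongest reply is that the entry records what the investigators expect, loosely placed under a formal heading, and that nothing turns on it. Part of this stands. A reader might infer a rule that p > 0.05 confirms the hypothesis, but the article writes no such rule. Its Discussion ties possible implementation to a lower DBI score, not to admissions or deaths being unchanged. What can be said is that a non-significant result is compatible with the stated alternative.

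The promised 95% interval for the proportions also counts. It covers two of the four outcomes and would show the imprecision. It does not correct the hypothesis, and it does not extend to the HRs.

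A reader might also infer that the trial would usually miss a clear rise in harm. That depends on the assumed rates: a 10-point rise from 10% or 20% has 73% or 56% power. Low power for modest effects is ordinary for secondary outcomes and would be the same under better wording. The figures show why non-significance must not be read as sameness; they do not measure the wording error itself.

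Nor does the DBI row conflict with the sample size, as a reader might suppose from its directional entry. It states an expected direction, the chi-squared test is conventionally two-sided, and 167 reproduces as a two-sided figure. No passage specifies one-sided testing.

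Finally, the superiority label in Study design is attached to general practitioner uptake of the recommendations. It does not by itself fix the form of the four secondary hypotheses, so the point rests on Table 3 alone. A separate analysis plan could add rules of interpretation, but it would have to depart from Table 3 to remove the overlap.

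**Conclusion.** The point holds as a defect in the stated hypothesis. For four secondary outcomes the alternative includes the null of the assigned test, a non-significant result fits it, and the non-inferiority claim it implies has no margin. This follows from the table itself and needs no assumption.

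The size of the practical risk does rest on assumptions. With the event rates tried here, power at 167 per arm is 16% to 28% for a 5-point rise and 48% to 73% for a 10-point rise. Modest rises would often go undetected, while larger ones from a low or moderate base would more often than not be seen. The primary analysis and the sample size are unaffected. The change should be made because it is cheap and governs what the trial may conclude about harm.

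**What to change.** - In Table 3, replace the four entries with a two-sided alternative that the outcome differs between arms.
- Report the HRs for residential care entry and mortality with 95% confidence intervals, as is already planned for the proportions.
- State that a non-significant result on these outcomes is inconclusive and will not be described as showing that they stayed the same.
- If a not-worse claim is wanted for any of them, pre-state its margin with a justification and base the claim on the upper confidence limit. At 167 per arm such a claim may be out of reach for tight margins.

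The cost is a change of wording in one table and in the rules for reporting. No test, sample size or data collection changes. The downside is that conclusions on these secondary outcomes become more modest.
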